These measurements will be spatially and temporally linked to satellite-derived meteorological data via GPS and timestamps, allowing for triangulation of heat exposure levels, adjustment for spatial variability, and improved resolution. The satellite-based temperature and humidity data retrieved for the entire pregnancy will be incorporated to complement individual-level measurements, supporting a more comprehensive assessment of cumulative heat exposure. By combining home and workplace measurements, this approach holistically captures heat exposure and its health impacts, ensuring a complete assessment of each woman’s complete environmental burden.

Personal heat exposure measurements will be captured using EasyLog USB temperature and humidity data loggers and wearable devices validated against the gold-standard Quest Temp°34 3M WBGT Monitor to calculate the WBGT heat index. The EasyLog USB data loggers will be deployed in a fixed location in the participant’s home for 24 hours to capture continuous area-level data. These devices are not worn; instead, they remain stationed in a participant’s key microenvironment throughout the monitoring period and are retrieved after for data download. Wearable devices in this study include the Fitbit Sense 2 smartwatch and iButton sensors. The Fitbit tracks maternal heart rate while the iButtons, one mounted below and another above the strap, measure the skin temperature and personal microclimate or ambient temperature, respectively. The iButtons are validated tools for capturing ambient temperature exposure in field settings and have been widely used in heat stress research
^
10

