### Sample size

This exploratory study will be powered primarily on multiple physiological and biochemical outcomes, rather than on clinical endpoints, many of which currently lack sufficient preliminary data to enable formal power calculations at the 5% significance level.

Primary outcomes:

Physiological and biochemical measures include maternal core body temperature, urine specific gravity, maternal cardiac output (USCOM), heart rate variability, and angiogenic ratio (sFlt-1/PlGF). Clinical outcomes include preterm birth (<37 weeks of gestation) and birth weight (grams).

Secondary outcomes:

Secondary endpoints comprise gestational age (weeks), small for gestational age (SGA), stillbirth, and additional placental and fetal biomarkers.

A total of 700 pregnant women will be enrolled to account for an anticipated attrition rate of approximately 15%, yielding an expected final sample of about 600 mother–baby dyads with complete follow-up. The majority of outcomes are continuous variables, which—following transformation to approximate normality, if required—will provide 80% statistical power at a two-sided significance level of α = 0.05 to detect a minimum difference of 0.23 standard deviations between high versus low heat exposure groups. This detectable effect size lies well within accepted thresholds for clinical relevance.

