### Statistical approach

The study team will implement a pre-specified Statistical Analysis Plan (SAP), finalized and published prior to database lock, to quantify associations between environmental exposures—heat, humidity, and ambient PM
_2.5_—and maternal, fetal, placental, and early lactational physiological outcomes. Analyses will follow a hierarchical framework (primary, secondary, exploratory) with clearly defined endpoints to manage multiplicity. Data will undergo standardized procedures for cleaning, validation, and coding. Patterns of missingness will be described, and multiple imputation will be applied where appropriate. All model assumptions (normality, collinearity, linearity) will be evaluated systematically.

Primary Analytical Framework – Mixed-Effects Models:

Given the longitudinal and multi-site design of the HiP-India study, mixed-effects models (LME, GLMM, GAMM) will constitute the core analytic approach.

Random effects: Site-level random intercepts will account for geographic and climatic clustering across Gurugram, Puducherry, and Chhattisgarh, while subject-level random intercepts and slopes will capture individual differences in heat-response trajectories.

Serial correlation: Autoregressive structures (e.g., AR(1)) will model correlations between repeated trimester-specific measurements.

Time-varying exposures: Trimester-specific heat exposure estimates will be modeled as time-varying covariates to assess both immediate and cumulative effects.

Model flexibility: Linear mixed models will be used for continuous outcomes (e.g., physiological measures, biomarkers), generalized linear mixed models for binary outcomes (e.g., preterm birth, SGA), and generalized additive mixed models where non-linear exposure–response patterns are expected.

Complementary Distributed Lag Non-Linear Models (DLNM):

DLNM will be employed to examine delayed and non-linear exposure–response relationships across gestation.

Lag structure: Lags will extend from enrolment through outcome ascertainment, capturing both short-term (≤28 days) and longer-term (up to ~20 weeks) effects.

Basis functions: Natural cubic splines with empirically derived knots will model non-linear exposure and lag responses.

Temporal alignment: Exposure windows will be aligned primarily by calendar date to preserve seasonal context, and secondarily by gestational age to identify sensitive developmental periods. Hybrid alignment approaches will also be considered.

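### Preterm birth is analysed as yes/no against heat exposure that may run up to delivery, so the outcome sets the length and calendar position of the exposure window

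*Protocol article*

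**What the plan says.** The Sample size section lists the primary outcomes and states: "Clinical outcomes include preterm birth (<37 weeks of gestation) and birth weight (grams". The Structured summary names the same two as the primary outcomes.

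The Statistical approach section then fixes four things that bear on preterm birth:

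- Model: "generalized linear mixed models for binary outcomes (e.g., preterm birth, SGA".
- Exposure in the core model: "Trimester-specific heat exposure estimates will be modeled as time-varying covariates to assess both immediate and cumulative effects".
- Lags in the complementary distributed lag models: "Lags will extend from enrolment through outcome ascertainment, capturing both short-term (≤28 days) and longer-term (up to ~20 weeks) effects".
- Alignment: "Exposure windows will be aligned primarily by calendar date to preserve seasonal context, and secondarily by gestational age to identify sensitive developmental periods".

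On the ambient series, the section on individual environmental exposures says: "The satellite-based temperature and humidity data retrieved for the entire pregnancy will be incorporated to complement individual-level measurements". Its purpose there is to assess cumulative exposure.

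The article names no time-to-event or risk-set model, no exposure window that closes before preterm births can occur, and no allowance for window length.

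**The concern.** Gestational age at birth determines both whether a birth is preterm and when an exposure window anchored at delivery ends. This has two effects.

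**Length.** A woman who delivers early accumulates fewer days of heat because she delivered early. Sums and counts of heat are then lower in preterm births, and heat looks protective.

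**Position.** The last weeks before a preterm birth fall at an earlier gestation and an earlier calendar date than the last weeks before a term birth. Recruitment is confined to seasonal windows, so a difference in date is a difference in temperature.

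At stake is a false association on a primary outcome, in a direction set by the choice of exposure summary. The plan also tests heat by season and stratifies by recruitment season, so an artefact that differs between warm and cool recruits could be read as acclimatisation.

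**Working it through.** **The plan's own figure.** The article gives no power or error figure for preterm birth. Its only calculation is for continuous outcomes: n per group = 2(1.960 + 0.842)² / 0.23² = 297, against 300 planned. It reproduces, with power 0.804 at 300 per group, and this point does not affect it.

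**Window length, by arithmetic.** Enrolment is at 11 to 13+6 weeks. The time from enrolment to 37 weeks is 37 − 11 = 26.0 weeks, down to 37 − 13.86 = 23.1 weeks. Every preterm birth has less than this and every term birth at least this much. At enrolment at 12.5 weeks, a 34-week birth has 21.5 weeks of exposure and a 40-week birth has 27.5.

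**Window position, by arithmetic.** 21.5 weeks is about 150 days and 27.5 weeks about 192 days.

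- Enrolled 1 May: delivery about 28 September (34 weeks) or 9 November (40 weeks). The preterm window falls earlier in the autumn cooling.
- Enrolled 1 November: about 31 March or 12 May. The preterm window falls earlier in the spring warming.
- Enrolled 28 February: about 28 July or 8 September. Both fall late in or after the hot season, so the direction among cool recruits depends on the local curve.

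**Null simulation.** From the protocol: 600 women, three sites, half warm and half cool recruits, the stated recruitment months, and enrolment at 11–14 weeks. Assumed:

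- Preterm rate 8, 13 or 18%.
- Sinusoidal temperature with site means of 25, 28.5 and 26 °C, amplitudes of 9, 3 and 6 °C, and peaks from late May to mid-June.
- Household SD 1 °C and daily SD 2 °C.
- Preterm births an exponential 2 weeks before 37 weeks (not below 26 weeks); term births normal, mean 39.2 weeks, SD 1.1.

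Preterm birth is drawn independently of temperature. The model is logit P(preterm) = site + recruitment season + b × exposure/SD, with 400 cohorts per rate. The nominal rejection rate is 5%, with Monte Carlo standard error √(0.05 × 0.95 / 400) = 1.1 points. Ranges are across the three preterm rates.

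| Exposure | Odds ratio per SD | Rejected |
|---|---|---|
| Degrees above 30 °C, summed, enrolment to delivery | 0.75 | 39–69% |
| Days above 32 °C, enrolment to delivery | 0.75–0.76 | 37–68% |
| Degrees above 30 °C, summed, 28 weeks to delivery | 0.40–0.42 | 91–99.8% |
| Mean, enrolment to delivery | 1.09–1.10 | 13–14.5% |
| Mean, 28 weeks to delivery | 1.03–1.07 | 14–17.5% |
| Mean, last 28 days | 1.75–1.81 | 49–77% |
| Mean, last 140 days | 1.09–1.10 | 11–13% |
| Mean or sum, fixed 14–26 weeks | 0.98–1.01 | 4.3–5.8% |

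**Sensitivity to the assumed curves.** Other three-site simulations at 13% preterm gave 0.66 to 0.68 for degrees above 30 °C summed to birth (rejected 83–89%) and 1.89 to 1.94 for the last-28-day mean (74–78%). Gurugram's windows alone gave 0.61 to 0.71 for the sum (77–89%). There, the last-28-day mean in warm recruits gave 1.77 to 2.15 per SD (84–99%). In cool recruits the odds ratio was 1.10–1.12 with a late-May peak and 0.50–0.62 with peaks from mid-June to July.

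**Planned adjustment.** The table already adjusts for site and recruitment season. Adding harmonics of conception date in the Gurugram runs raised rejection for the heat sum to 100%: once the start date is fixed, what varies is largely the length of gestation.

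**Risk-set model on the same kind of null data.** Weekly hazard for weeks 26–36, logit h(w) = w + w² + site + season + b × exposure up to week w, 300 cohorts at 13% preterm. The odds ratio was 1.00, with rejection of 4.0% for cumulative heat above 30 °C and 5.0% for the prior 28-day mean.

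**The case against.** Five arguments stand against this point.

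1. **The binary model is not the fault.** The model sentence says nothing about the exposure window, and a logistic model with a closed window holds its level (last row of the table). This stands. A reader might infer that the mixed model must be dropped for preterm birth; the calculations do not support that.
2. **The lag sentence is capped and names no outcome.** It belongs to the complementary models, and the section on placental biomarkers, where these models also appear, uses them for another purpose. Taking delivery as the end of the window for preterm birth is therefore a reading, though the natural one for an outcome known only at birth. The cap matters: from 12.5 weeks, any birth after 32.5 weeks has a full 20-week window. In one simulation only 1.6% of women had less, and capped degree-days gave 0.99 with 14% rejection. It would thus be wrong to say that the plan's stated lag range must show heat as protective. A residual bias from window position remains.
3. **Visit readings are not anchored at delivery.** This stands. In a null simulation, readings at the fixed visits gave odds ratios of 1.00 to 1.01 and rejection of 4.4 to 5.6%, with missing third visits dropped. The exposed part is the cumulative and lagged use of the ambient series.
4. **The analysis plan may settle the window.** It may. But the published text already sets lags running to outcome ascertainment and asks for cumulative effects, so an analysis plan that simply follows it inherits the problem.
5. **The study is exploratory and powered on physiological measures.** True, and it tempers the urgency. It does not excuse error rates this far above nominal for a listed primary outcome.

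A reader might also object that subject-level random effects and AR(1) terms cannot be estimated with one preterm outcome per woman. The text ties those terms to individual trajectories and repeated trimester measurements, so it does not place them in this model.

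**Conclusion.** The concern holds in a limited form. As written, the protocol allows preterm birth to be regressed on heat whose window ends at delivery, and nothing in the text closes that window or compares women at the same gestation.

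The size depends on the exposure summary. Uncapped sums above 30 °C from enrolment to birth are biased towards protection, and the last-28-day mean towards harm; both reject far above 5%. Long-window means and lags capped at about 20 weeks are biased much less, with rejection about 11 to 14% in most runs (9 to 29% for the last-140-day mean with Gurugram's windows alone). Early and mid-pregnancy visit readings are unaffected.

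A reader might infer a fixed pattern of opposite biases in warm and cool recruits. Only the warm-recruit direction was stable; the cool-recruit direction changed with the assumed date of peak temperature.

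The mechanism follows from the protocol's wording and simple arithmetic. The magnitudes rest on assumed temperature curves, preterm rates and gestational-age distributions, none of which the article gives.

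**What to change.** State in the protocol and the analysis plan, for preterm birth:

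- **Early and cumulative exposure.** Keep the binary mixed model, with an exposure window of fixed gestational length that closes before preterm births occur (for example, enrolment to 26–28 weeks), among women still pregnant when it closes.
- **Late and immediate exposure, including lagged effects.** Use a gestational-week risk-set model (discrete-time hazard or Cox) censored at 37 weeks, with exposure only up to each at-risk week and adjustment for calendar time.
- **Exclusion.** Do not relate preterm birth to sums, counts or means anchored at delivery, and qualify the lag sentence accordingly.

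The mixed model need not be deleted. The cost is a change of wording, some analysis work and a person-week data set. Birth dates, ultrasound dating and the satellite series it needs are already planned, and the change can be made before database lock.

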## Abstract

**Background:**

Extreme heat exposure — defined as sustained ambient temperatures exceeding local thresholds — has been associated with several adverse pregnancy outcomes, including preterm birth, stillbirth, gestational diabetes and small for gestational age. However, the mechanisms linking environmental heat to these outcomes, and the biological markers that signify individual vulnerability, are not well understood. We present the protocol for a prospective cohort study within the Heat in Pregnancy-India consortium (HiP-India). This study aims to characterise the physiological and pathophysiological responses of the mother, placenta, and fetus to varying levels of temperature, humidity, and air pollution exposure, and to identify the critical windows and mechanisms of heat-related risk during pregnancy.

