### Maternal haemodynamic assessment

It is hypothesised that the effects of heat exposure on the maternal circulation may depend on the gestational age at exposure. Specifically: (i) early pregnancy maternal hemodynamic disruptions will directly impact early placental development and increase the risk of preeclampsia and other hypertensive disorders of pregnancy, whilst (ii) mid-to-late pregnancy hemodynamic changes may influence cardiovascular load, leading to maternal cardiovascular maladaptation, which could lead to changes in the uteroplacental circulation.

Maternal hemodynamic status, including pulse, blood pressure, Cardiac output (CO), and total peripheral vascular resistance (TPVR), will be measured each trimester using the USCOM 1A® pulsed wave monitor. The USCOM 1 A is a non-invasive, portable machine that utilises continuous wave Doppler technology and it has been validated for use in pregnancy
^
11
^. 

All examinations will be undertaken under standardised conditions using the same equipment in each site. Women will be asked to sit quietly for 5 minutes before the commencement of the investigations. A brachial blood pressure reading will be recorded using the appropriate cuff size from the right arm of the participant. Participant height (cm) will be measured during enrolment, and weight (kg) will be recorded at the time of each assessment. Two USCOM readings will be taken at an interval of 1 minute apart, with the average of the two readings used for analysis. Participants with abnormal hemodynamic results will be referred to a hospital physician for appropriate care, facilitated by the study staff.

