### Placental circulating biomarkers

It is hypothesised that exposure to elevated environmental temperatures may impair placental function, leading to measurable alterations in circulating angiogenic and inflammatory biomarkers. A critical component of this dysfunction may involve changes in the molecular cargo of placental small extracellular vesicles (sEVs), which play a central role in mediating cell-to-cell communication during pregnancy
^
23–
25
^. Disruption of this signalling network may adversely influence maternal immune modulation, vascular function, and placental development, ultimately contributing to complications such as preterm birth, fetal growth restriction, and stillbirth. Building upon findings from the retrospective GARBH-Ini cohort (WP1a;
Figure 1), this prospective study aims to validate key placental biomarkers and elucidate mechanistic pathways implicated in heat-induced pregnancy complications. Environmental temperature exposure will be quantified using high-resolution spatiotemporal models and stratified across participants from rural and peri-urban settings in India.

Maternal venous blood samples collected at predefined gestational windows will be utilized to assess the cumulative and time-specific effects of chronic heat exposure on placental physiology. Distributed lag non-linear models (DLNM) and generalized additive models (GAM) will be used to identify critical windows of gestational vulnerability to heat exposure. Based on model-derived exposure classifications, maternal samples will be stratified into high and low exposure groups to quantify surrogate markers of placental stress. Key surrogate markers of placental stress will be quantified using immunoassay-based platforms. These include angiogenic markers (sFlt-1
^
26
^, PlGF, VEGF
^
27
^, PAPP-A
^
28
^), hormonal markers (progesterone), and inflammatory mediators (C-reactive protein [CRP], alpha-1-acid glycoprotein [AGP]
^
29,
30
^). This multi-marker approach will allow for a comprehensive assessment of placental health in the context of heat exposure. In addition, proteomic candidates previously identified in the retrospective GARBH-Ini dataset (WP1a;
Figure 1) will be evaluated in this prospective cohort to confirm differential expression in response to varying levels of heat exposure and various pregnancy outcomes. Additionally, functional validation of selected protein candidates will be conducted using

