**Figure 3. f3:**
[figure not shown]
Tentative DAG to handle confounders in the analysis.

PM
_2.5_ Treatment Strategy:

Primary analysis: PM
_2.5_ will be modeled as an effect modifier (Heat × PM
_2.5_ interaction).

Secondary analysis: If significant interaction is not detected, PM
_2.5_ will be adjusted as a confounder in sensitivity models.

Justification: Both exposures may exert synergistic biological influences on maternal thermoregulation and hemodynamics.

Prespecified Interactions and Stratifications:

Interactions to be formally tested include:

Heat × PM
_2.5_ (synergistic effects on maternal hemodynamics), Heat × Site (climate adaptation differences), Heat × Season (acclimatization effects), Heat × Occupation (differential vulnerability by work environment), and Heat × Housing Quality (thermal protection efficacy).

Stratified analyses will be conducted by site (Gurugram, Puducherry, Chhattisgarh), recruitment season (warm vs. cool), occupation (high-risk vs. lower-risk), housing quality (traditional vs. modern materials), and gestational timing (early vs. mid vs. late pregnancy enrolment).

Mediation and Sensitivity Analysis Framework:

The study design facilitates mediation analysis through temporally aligned data collection, with personalized exposure monitoring, blood pressure measurement, biomarker sampling, and clinical assessment conducted synchronously at three points across pregnancy. This alignment strengthens the exposure → mediator → outcome temporal sequence and reduces bias from measurement misalignment.

To address unmeasured confounding, the analysis will consider negative control approaches using biomarkers or outcomes theoretically unrelated to the heat–hemodynamic pathway, supplemented by mediational E-values to quantify the magnitude of unmeasured confounding required to alter results. The multi-site structure enables leveraging geographic and seasonal variation as natural experiments to test mediation assumptions.

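### The complementary distributed-lag models start their lags at enrolment, so they omit nearly all first-trimester exposure, and the lag limit of about 20 weeks does not fit birth outcomes

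*Protocol article*

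**What the plan says.** The protocol article, Statistical approach, introduces the DLNM as a complement to the mixed-effects models: "DLNM will be employed to examine delayed and non-linear exposure–response relationships across gestation". Its lag structure is: "Lags will extend from enrolment through outcome ascertainment, capturing both short-term (≤28 days) and longer-term (up to ~20 weeks) effects". On alignment it says: "Exposure windows will be aligned primarily by calendar date to preserve seasonal context, and secondarily by gestational age to identify sensitive developmental periods". Hybrid alignment is also to be considered.

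Under Inclusion criteria, recruitment is limited to 11 to 13+6 weeks by crown-rump length (CRL).

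Finding critical windows is part of the study's purpose. The abstract's Background gives the aim "to identify the critical windows and mechanisms of heat-related risk during pregnancy". Under Placental circulating biomarkers, DLNM together with generalised additive models "will be used to identify critical windows of gestational vulnerability to heat exposure". Early pregnancy is one of the windows hypothesised: under Maternal haemodynamic assessment, "early pregnancy maternal hemodynamic disruptions will directly impact early placental development". The section on fetal and placental ultrasound likewise links first-trimester uterine artery flow to poor trophoblast invasion.

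Exposure data for that period will exist. Under Individual environmental exposures: "The satellite-based temperature and humidity data retrieved for the entire pregnancy will be incorporated to complement individual-level measurements".

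Under Prespecified Interactions and Stratifications, one planned stratification is by "gestational timing (early vs. mid vs. late pregnancy enrolment").

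**The concern.** A distributed-lag model can estimate effects only at the lags it contains. If the lag axis opens at enrolment, conception to 11-14 weeks is outside the model, although the hypotheses place early placental harm there. The model could then neither show nor rule out an early window. Exposure before the window is left unmodelled, and where it is correlated with later exposure through season, part of an early effect may appear as a mid- or late-pregnancy effect.

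The same sentence gives two limits: from enrolment to the outcome, and about 20 weeks. For birth weight and preterm birth, both listed as primary clinical outcomes under Sample size, the two limits differ by several weeks. An analyst cannot tell which governs.

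**Working it through.** **Inputs.** From the protocol: enrolment at 11 to 13+6 weeks (13+6 = 13.86); visits at 11-14, 18-22 and 30-34 weeks (Table 1); longest lag about 20 weeks; preterm birth defined as before 37 weeks. Assumed, because the protocol gives no distribution of gestational age at birth: term births at 37-41 weeks, and preterm births illustrated at 32 and 36 weeks. Gestational age is counted from the last menstrual period (LMP).

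**Step 1: where the 20-week figure fits.** Time from enrolment to outcome = gestational age at outcome − gestational age at enrolment. For the 30-34 week visit this runs from 30 − 13.86 = 16.1 to 34 − 11 = 23.0 weeks, with a midpoint of about 19.6. So the plan's figure is reproduced for the last antenatal visit.

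**Step 2: other outcomes.** The last column is gestational age at outcome − 20.

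| Outcome | Enrolment to outcome (weeks) | Week at which a 20-week lag opens |
|---|---|---|
| Visit at 18-22 weeks | 4.1-11.0 | before pregnancy, up to week 2 |
| Visit at 30-34 weeks | 16.1-23.0 | 10-14 |
| Birth at 32 weeks | 18.1-21.0 | 12 |
| Birth at 36 weeks | 22.1-25.0 | 16 |
| Birth at 37 weeks | 23.1-26.0 | 17 |
| Birth at 40 weeks | 26.1-29.0 | 20 |
| Birth at 41 weeks | 27.1-30.0 | 21 |

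For term births, the span from enrolment to outcome is therefore 23.1-30.0 weeks, which is longer than the stated maximum.

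**Step 3: share lost if the enrolment start governs.** Of a 40-week pregnancy: 11/40 = 27.5% for the earliest enrolment and 13.86/40 = 34.6% for the latest. Of the first 14 weeks: 11/14 = 79% to 13.86/14 = 99%. Counted from conception (two weeks later), the share is (11 − 2)/38 = 24% to (13.86 − 2)/38 = 31%. For outcomes at the first visit, the window has almost no length: at most 13.86 − 11 = 2.9 weeks.

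**Step 4: share lost if the 20-week maximum governs.** Everything before weeks 17-21 is outside for term births; at 40 weeks that is 20/40 = 50%. For births at 32-36 weeks the cut-off is weeks 12-16. If both limits apply, the window opens at the later of the two, so for a birth at 32 weeks it opens at 12 to 13.9 weeks. A fixed maximum also makes the weeks covered depend on gestational age at birth: from week 16 for a birth at 36 weeks, but from week 20 for one at 40 weeks.

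**Step 5: the enrolment strata.** Every participant enrols between 11 and 13+6 weeks, so the mid- and late-enrolment strata contain no women.

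**The case against.** The DLNM is only complementary. The core analysis is the mixed-effects model, which takes trimester-specific exposure as a time-varying covariate for immediate and cumulative effects, so first-trimester heat does enter the main analysis. Window-finding for the biomarkers is assigned to generalised additive models as well as DLNM. The study describes itself as exploratory, and the analysis plan is still to be finalised before database lock. All of this stands, and it limits the point to what the DLNM can locate. It does not remove the point, because the article states the start of the lag explicitly and a trimester-level estimate cannot resolve windows within the trimester.

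Four stronger readings are tempting and are not supported:

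- **The study ignores the first trimester.** The core models contradict this.
- **Birth outcomes always lose everything before about week 20.** That holds only if the 20-week maximum governs and the birth is near 40 weeks. If the enrolment start governs, the loss ends at 11 to 13+6 weeks.
- **Early effects will be attributed to later exposure.** The protocol gives no correlation between early and late exposure, and season or recruitment timing is in the adjustment set. Misattribution is possible but not shown.
- **Primary alignment by calendar date is an error.** The plan already assigns gestational-age alignment to the search for sensitive periods. Which alignment ranks first is a matter of choice.

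**Conclusion.** The point holds for the complementary DLNM. With lags starting at enrolment, these models omit 28-35% of a 40-week pregnancy counted from LMP, including 79-99% of the first 14 weeks. That is a period the protocol hypothesises to be critical and for which it retrieves satellite temperature and humidity. These shares follow from the inclusion criteria; only the 40-week denominator is assumed.

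The two limits in the lag sentence agree for the 30-34 week visit but conflict for term births, where enrolment to outcome is about 23-30 weeks. The further loss from a 20-week maximum depends on that reading and on the assumed week of birth.

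The stratification by early, mid or late enrolment is a separate defect, and it cannot be carried out under the inclusion criteria. No data are lost by any of this; the repair is to the analysis specification.

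**What to change.** - Run the DLNM lags back to the CRL-dated start of pregnancy, using the satellite series.
- Set the maximum lag by outcome: back from the visit date for visit outcomes, back from birth for birth outcomes, and for preterm birth, over exposure up to the end of the at-risk period. State this in place of the single 20-week figure.
- Use the gestational-age alignment already planned for the questions about windows.
- Separately, replace the strata by timing of enrolment with trimester of exposure.

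The cost is revised wording in the analysis plan and a few more spline degrees of freedom on the lag axis. Exposure before enrolment will rest on satellite data alone and so will be coarser than exposure after it; this should be stated when early windows are reported.
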